#### Recruitment

There will be a total of 60 participants split between the experimental and control subgroups (see Figure 1).The recruitment of the 30 experimental patients, conducted by psychiatrists and clinical psychologists, will take place in the outpatient clinic and day hospital of the Addictions Unit of the Hospital Clínic de Barcelona. The usual health care professionals for patients with anxiety symptoms will refer the selected patients to the research team who will assess whether the selected patients meet the eligibility criteria. The 30 healthy control participants will be recruited using brochures distributed by the Faculty of Medicine at the University of Barcelona, as well as through social media.

**Figure 1 figure1:**
[figure not shown]
Study recruitment diagram.

Patients deemed eligible for the study will be contacted by the research team and will have the study explained to them. They will be given a sheet with instructions for proper usage of the Fitbit device (ie, how to load it, how to connect to the app, etc). Informed consent will be given after a full explanation of the trial, including the trial’s use of data assets and potential liabilities.

### Study Procedures

Participants will complete the study phases as described in the following sections.

#### Initial In-Person Visit: First Visit

Once deemed eligible by the research team, participants who meet the requirements for the experimental group, as well as the volunteer control participants, will be called to the Hospital Clínic de Barcelona. The first visit will last approximately one hour and will include an explanation of the project to the participants with time for them to ask questions and clarify any doubts. We will explain to the participants’ their rights and obtain their informed consent in the presence of the research team. We will also explain the measurement of the following variables: age, gender, education level, marital status, symptoms of anxiety (measured with the STAI), symptoms of depression (measured with the BDI-II), evaluation of alcohol use disorder (measured with the AUDIT), use of medication, medical comorbidities, and substance use. Those experiencing current medication or substance abuse will not be considered for the healthy control group.

Once the variables are profiled, each participant will be instructed to download the HumanITcare platform app and will receive their data encryption code and password. The app will use the participants’ mobile phone sensors to collect and consolidate data, which are then sent to the research team for evaluation. A Fitbit device will also be provided and each participant will be informed of their obligation to return the device once the study is completed. For proper operation of the Fitbit, participants will be instructed to access the Fitbit app through their personal email and to specify their age, sex, weight, height, and date of birth. This app complies with data protection laws.

Physiological and behavioral data from the participants’ smartphone devices will be compiled in the HumanITcare servers and will be transmitted, along with the data collected in the Fitbit servers, to a separate server available to the research team, which assigns each participant a unique, randomized character code that functions as a profile name (eg, mt1e45al). The data collected through the HumanITcare app and servers and the Fitbit servers for each participant will be represented by this 8-digit code in order to protect each participant’s privacy.

#### Weekly Assessment of Depression and Anxiety Symptoms

Patients will receive a notification from the HumanITcare app once per week reminding them to respond to the three questionnaires—STAI, BDI-II, and AUDIT [15]—available on the HumanITcare app. This will result in a total of four evaluations throughout the duration of the 1-month study period.

#### Noncontact Visits

Research assistants will perform supervision of participants’ data and will monitor whether participants are answering the three weekly questionnaires through the HumanITcare platform. Research assistants will make reminder calls to participants if they are not responding to the questionnaires, in which case the factors that have influenced nonresponse will be explored. All of this data will be recorded.

#### Final In-Person Visit: Second Visit

The investigator shall summon each participant to the Hospital Clínic de Barcelona to return the borrowed Fitbit device. For participants in both groups, data will be collected regarding user experience with the app through an adaptation of the System Usability Scale (SUS) [17] and the Post-Study System Usability Questionnaire (PSSUQ) [18].

Once the study has been completed, data analysis and data processing will follow. After the statistical analysis is complete, we will proceed to the discussion and interpretation of the results and the writing of a scientific article that outlines the findings.

### HumanITcare App

HumanITcare is a Spanish company that has developed an Internet of Things (IoT) platform (HumanITcare platform) as well as a mobile app (HumanITcare app) for the collection and analysis of the daily data of the participants. The HumanITcare app is an Android and iOS app developed by HumanITcare with the intent of collecting mobile phone sensor data for clinical use. The app continuously collects and stores users’ sensor data within the HumanITcare app servers, automatically uploading the data collected by the sensors to the HumanITcare servers when connected to Wi-Fi. This allows for constant gathering of sensor data regardless of the quality of network service available at the time; this also ensures that mobile data fees are not charged to users.

The HumanITcare platform ensures anonymity for users by utilizing the SHA (Secure Hash Algorithm)-256 hashing algorithm to encrypt the data collected by users’ mobile phone sensors. Furthermore, all of the data collected for each participant are only recognizable by a randomized 8-character code (eg, mt1e45al) assigned to each participant, ensuring that the data are anonymous. The data collected by the HumanITcare app will be evaluated in tandem with data collected by a Fitbit wearable device; however, the app offers a wider breadth of sensors. The passive data types collected by the app and the Fitbit wearable device are represented in Textbox 1.

Passive sensor data collected by the HumanITcare app and the Fitbit device.Mobile phone sensors utilized in the HumanITcare app:AccelerometerBluetoothCall logText logMobile phone identifierGPSPower state: battery levelPower state: charging eventPower state: screen on or offWi-Fi connectionFitbit sensors utilized:Heart rate monitorSleep monitorAccelerometer

### Outcomes

#### Primary Outcome: Sensor Data Accuracy and Efficiency

The symptoms of anxiety and alcohol use disorder presented to the research team will be derived from the algorithm calculated from data collected by the HumanITcare platform (ie, app) and the Fitbit devices. These symptoms will be compared with the diagnoses provided by the status quo, *gold standard* questionnaires—the STAI [13] and the DSM-5 [16]—to determine the feasibility and efficiency of using objective sensor data in place of the current subjective methods of diagnosing mental health disorders. This will be done in a two-step process: first, by determining the relationship between the individual types of data tracked by sensors (eg, distance traveled and sleep schedule) and levels of anxiety and alcohol use disorder symptoms as presented by the questionnaires; and second, by using a mathematical model to estimate questionnaire scores by solely using the data collected by sensors (see Table 1). The primary outcome will be the efficiency of the developed algorithm’s ability to predict disorder symptoms.

**Table 1 table1:** Data collection by sensors compared with questionnaires.

Type of data being collected		Method of data collection

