### Study Objectives

Due to emerging research on digital biomarkers and the accuracy of passive monitoring of data in patients with mental health disorders, we propose to conduct the REMOTE Study among a group of 60 participants split into two subgroups of 30 participants each This study will be conducted in the Addictions Unit at the Hospital Clínic de Barcelona. The primary objective of this study is to analyze the digital physiological patterns of two groups of participants—one group with symptoms of anxiety disorder and alcohol use disorder and one healthy control group without these disorders—using data collected from a mobile device (ie, smartphone) and a wearable sensor (ie, Fitbit). The data will be collected from the sensors through the HumanITcare platform. The data will then be compared with the symptoms validated in clinical questionnaires, which participants will complete four times over the course of the study, in order to determine whether the use of sensor data is an efficient and accurate means of presenting objective diagnoses rather than the subjective diagnoses of the status quo.

The secondary objective of this study is to analyze usability and patient satisfaction with the data collection service provided by the app and to explore the feasibility of this approach in clinical practice.

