## Methods

### Design

#### Overview

This study is a case-controlled, prospective study consisting of two groups: one group of healthy control individuals who do not have symptoms of alcohol use disorders or anxiety and one experimental group that meets the selection criteria described in the Study Population and Setting section. Participants in both groups will be matched for age and sex, since both can be confounding factors regarding usage patterns of electronic devices. Both groups will receive mobile and wearable sensors that will track their physiological and behavioral activity over the course of 1 month. Both groups will also take the State-Trait Anxiety Inventory (STAI) [13], the Beck Depression Inventory-II (BDI-II) [14], and the Alcohol Use Disorders Identification Test (AUDIT) [15] once per week through the HumanITcare app downloaded on their phones. Participants will be instructed on the use of the app during the initial visit, along with receiving their wearable sensors (ie, Fitbits). The data will be monitored by the research team through an online, encrypted compilation of participants’ data.

The HumanITcare platform allows for the collection of data from the participants; the platform also provides a source of data for the researchers to verify that each participant’s data are being collected appropriately and that the Fitbit devices are working properly. The HumanITcare app that participants download to their phones collects data from the phones and sends them to the HumanITcare platform. As stated above, the app sends notifications to the participants once a week to remind them to complete the questionnaires. Also, it provides a *help* button so they can contact the researchers if needed (see the HumanITcare App section below).

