#### Study Population and Setting

The study will be conducted at the Hospital Clínic de Barcelona and is a single-center national study. Experimental participants will be drawn from the outpatient clinic at the Addictions Unit of the Hospital Clínic de Barcelona, and control group participants will be drawn from random volunteers recruited through fliers and social media.

The research team members at the Hospital Clínic de Barcelona Addictions Unit will be tasked with finding eligible subjects for the experimental group. The inclusion criteria for the experimental group participants are as follows: must be between the ages of 18 and 70 years; must have knowledge and daily use of new technologies; must have an alcohol use disorder, based on the Diagnostic and Statistical Manual of Mental Disorders, 5th Edition (DSM-5) [16]; must have significant anxiety symptoms (STAI score >33rd percentile); and must have been informed about the study and signed the data processing consent form. Potential experimental group participants are not eligible if they meet any of the following criteria: their mobile device is not compatible with the Android mobile operating system (OS); they have a diagnosis of affective disorder, based on the DSM-5; they have cognitive deficits that prevent proper participation; or they actively consume other substances, in addition to alcohol, except nicotine.

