### Data Analysis

#### Overview

For each participant, we will collect data through a Fitbit and smartphone device, as well as written data through the form of questionnaires. The devices will offer insight into the physiological responses and changes within participants, which provides a more objective side of the data. For example, the heart rate monitor will report the intensity of one’s heartbeat and could suggest symptoms of anxiety. Additionally, the smartphone GPS will report a participant's movement and, therefore, insight into one’s daily energy or lethargy.

The written responses through questionnaires will give a subjective account of the participants’ anxiety or alcohol use disorder symptoms. An example of this is the STAI, which asks for a scalar rating on one’s feeling of lethargy. Using the data from the Fitbit and smartphone devices, plus the data from the questionnaires, we will determine any correlation.

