#### Statistical Methods

The statistical analysis will be carried out as described in this section. Data collected from Fitbit devices, smartphones, and surveys from both groups will be interpreted with descriptive statistics. For the entire group, including all experimental and control participants, the mean and median will be calculated to determine the central tendencies. Next, we will find the standard deviation and range of the data to determine the variability within the dataset. The same process will be done for each group—experimental and control—individually, for the purpose of between-group comparison. The data will also be split and compared based on the source of the data: device information versus survey information.

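### Anxiety and alcohol use disorder occur together in every case and in no control, so unless a within-group relation is required, a sensor that only marks case status can appear to predict symptom scores

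*Protocol article*

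**What the plan says.** Study Objectives in the protocol article sets the comparison as "one group with symptoms of anxiety disorder and alcohol use disorder and one healthy control group without these disorders". The Design overview describes the controls as "healthy control individuals who do not have symptoms of alcohol use disorders or anxiety". Under Study Population and Setting, a case needs both a DSM-5 alcohol use disorder and a STAI score above the 33rd percentile. There is no group with anxiety alone or alcohol use disorder alone. Matching is on age and sex.

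Under Recruitment, "There will be a total of 60 participants split between the experimental and control subgroups", 30 in each. Both groups wear the sensors and complete STAI, BDI-II and AUDIT weekly, which gives four evaluations per person.

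The primary outcome has two steps. The first is "determining the relationship between the individual types of data tracked by sensors" and questionnaire levels of anxiety and alcohol symptoms. The second is a model that estimates questionnaire scores with sensor data as its only input. The result is to show whether sensors could replace present diagnostic methods.

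The Data Analysis overview adds: "Using the data from the Fitbit and smartphone devices, plus the data from the questionnaires, we will determine any correlation". Statistical Methods gives means, medians, SDs and ranges, first "For the entire group, including all experimental and control participants" and then for each group so that the groups can be compared. It also says that device and survey data will be separated and compared. Neither section names the analysis population for the correlation or the model.

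**The concern.** Because the two conditions enter and leave the sample together, STAI, AUDIT and case status tend to rise and fall together across the 60 participants. Patients of an addictions unit and volunteers recruited by flier and social media can also differ in treatment, employment, daily routine and phone habits. Any sensor feature that picks up such a difference will tend to correlate with STAI and AUDIT when both groups are analysed together, even if it carries no information on how anxious a given patient is.

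Matching on age and sex does not remove this. A model restricted to sensor inputs has no term for case status, so it can gain apparent accuracy simply by recovering group membership. The primary conclusion, that sensors estimate anxiety and alcohol symptoms, could then be reached with no such relation in either group. The pooled data alone could not say which of the two conditions a sensor reflects.

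**Working it through.** **No figure of the plan to reproduce.** The article gives 60 participants (30 + 30) without alpha, power or effect size, and this check does not depend on how 60 was chosen.

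**Why both groups together is the natural reading.**
- The model takes sensor data only, so case status is not an input.
- The algorithm is meant to reproduce diagnosis, so it has to work on people with and without the conditions.
- DSM-5 is one of the reference standards. Alcohol use disorder is present in every case and meant to be absent in every control, so agreement with it can be judged only across groups.
- The by-group work that is described consists of summary statistics.

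**Inputs.** From the article: 30 per group. Assumed, because the article gives none of them: two-sided 5% level, one averaged value per person, normal data with equal SDs, no sensor-STAI relation within either group, a case-control gap of D SDs in STAI and d SDs in the sensor.

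**Formula.** For two equal groups, each variance gains a between-group part (d²/4 or D²/4) and the covariance is dD/4, so

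r = (dD/4) / √[(1 + d²/4)(1 + D²/4)].

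For D = 2, d = 1: r = 0.5 / √(1.25 × 2) = 0.5 / 1.581 = 0.32.
For D = 1, d = 0.5: r = 0.125 / √(1.0625 × 1.25) = 0.125 / 1.152 = 0.11.

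**Rejection rates**, from simulated trials of 30 + 30 (20,000 or more per scenario):

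| STAI gap D (SD) | Sensor gap d (SD) | Pooled r | Pooled p<0.05 | Group-centred p<0.05 |
|---|---|---|---|---|
| 2 | 0 | 0.00 | 5% | 5% |
| 1 | 0.5 | 0.11 | 13% | 5% |
| 1.5 | 1 | 0.27 | 57% | 5% |
| 2 | 1 | 0.32 | 73% | 5% |
| 2 | 1.5 | 0.42 | 96% | 5% |

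An analysis of cases only also stays at about 5% in every row. The formula is the same for AUDIT, with D as the gap in AUDIT.

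**Precision after the change.** By Fisher's z, the correlation detectable with 80% power is tanh[(1.960 + 0.842)/√(n − 3)].
- n = 60: tanh(2.802/7.550) = 0.35.
- n = 30: tanh(2.802/5.196) = 0.49.

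The Discussion reports one dropout, from the experimental group. With n = 29 and n = 59 the figures are 0.50 and 0.36.

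**The case against.** **Pooling is inferred.** A reader might take the whole-sample wording in Statistical Methods as a statement that the model is fitted to both groups together. That sentence covers only the mean and median, and the next one the SD and range. The article does not say that the sensor-score relation is pooled, and an analysis plan that is not shown could add a group term or a cases-only analysis. This stands, and it lowers confidence. It does not remove the point: the group structure, the sensor-only model and the diagnostic aim are all fixed in the article, and none of them requires a relation within group.

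**The between-group signal is partly the aim.** Study Objectives asks for the patterns of the two groups, and a diagnostic algorithm cannot use case status as an input. A sensor that separates patients from healthy volunteers is therefore a legitimate finding. This also stands, so the documents do not support replacing the primary outcome outright. The problem arises when that separation is reported as tracking anxiety or alcohol symptoms, or as diagnosis.

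**The size is unknown.** A reader might conclude that a sensor marking case status will appear to predict anxiety. The documents support only that it can. They give no gaps, an entry threshold at the 33rd percentile may leave a modest STAI difference, and a sensor that does not differ by group stays at 5%.

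**Further faults might be inferred.** Four weekly scores could suggest that repeated records will be treated as independent, and the aim of replacing diagnosis could suggest that predictive values will be reported from a sample that is half cases. The article describes neither, so neither is part of this point.

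**This is a declared pilot.** That accounts for the small sample. It does not license a symptom-specific or diagnostic conclusion from a contrast that cannot isolate it. The limitations discussed (depression, Android phones and socioeconomic status, age and familiarity) do not mention this one.

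**Conclusion.** The concern holds in a limited form. As described, the primary outcome can be met by a sensor that only distinguishes cases from controls. With no relation in either group, the chance of a significant pooled correlation runs from about 13% to 96% across the assumed gaps with a sensor difference, against about 5% when group-centred. These figures rest on the inferred use of both groups together, on one averaged value per person, and on gaps that the article does not supply.

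Adjusting for group removes the between-group artefact but does not by itself separate anxiety from alcohol severity among cases. An anxiety-specific claim needs more than a group term.

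**What to change.** In Outcomes and in Statistical Methods:

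- Require that any claim that sensors track anxiety or alcohol symptoms rest on the sensor-score association, and on score prediction, adjusted for group and within cases. Use the four weekly scores in a mixed model with a random participant intercept.
- For a claim specific to anxiety, also adjust for AUDIT.
- Report case-versus-control discrimination as a separate result, labelled as such.
- In Study Objectives and in the primary outcome, narrow the statements on objective diagnosis and on replacing present methods to discrimination of patients with both conditions from healthy volunteers.

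No new data are needed. According to Results, collection had ended and processing was still under way at publication, so the cost is wording and modest extra modelling. The headline figures may be less favourable. Precision falls within cases: a correlation of about 0.49 is detectable with 30 cases, against 0.35 with all 60. The report should state this so that a null within-case result is not over-read.

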**Sensor data: to be used to calculate estimation algorithm**		
	Sleep pattern	Monitored using a cardiac activity sensor and the Fitbit watch given to participants at the initial visit
	Rapid eye movement (REM) sleep time	Monitored using the Fitbit motion sensor and cardiac activity sensor
	Heart rate	Monitored using the Fitbit sensor
	Step count	Monitored by compiling each participant’s daily step count using an accelerometer, smartphone GPS services, and Fitbit motion sensor
	Distance travelled	Monitored using the GPS services of each participant’s smartphone via the HumanITcare app
	Mobile device usage	Monitored by determining the time frames in which there was a presence or absence of signals from each participant’s device via the HumanITcare app
	Sociability: number of incoming and outgoing calls and text messages	Monitored by the number of incoming and outgoing calls and text messages from each participant’s smartphone via the HumanITcare app

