**Questionnaire data: to be tested against estimation algorithm**		
	Self-reported anxiety symptoms	Assessed via the State-Trait Anxiety Inventory (STAI); participants receive STAI scores ranging from 0 (lowest number of symptoms) to 60 (greatest number of symptoms), which are then transformed into percentiles according to age and sex
	Self-reported depression symptoms	Assessed via the Beck Depression Inventory-II (BDI-II); participants receive BDI-II scores ranging from 1 to 63: a score of 0-13 indicates minimal depression, 14-19 indicates mild depression, 20-28 indicates moderate depression, and 29-63 indicates severe depression
	Self-reported alcohol use symptoms	Assessed via the Alcohol Use Disorders Identification Test (AUDIT); participants receive AUDIT scores ranging from 0 to 40: a score of ≥8 is associated with harmful or hazardous drinking and a score of ≥13 in women or ≥15 in men is likely to indicate alcohol dependence

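### The primary outcome judges the algorithm on sensor data alone, with no age-and-sex benchmark to show what the sensors add

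*Protocol article*

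**What the plan says.** The article's section on the primary outcome sets two steps. Step 1 relates individual sensor measures to symptom levels. Step 2 proceeds "by using a mathematical model to estimate questionnaire scores by solely using the data collected by sensors". The section then fixes the criterion: "The primary outcome will be the efficiency of the developed algorithm’s ability to predict disorder symptoms".

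Table 1 lists the inputs under "Sensor data: to be used to calculate estimation algorithm": sleep pattern, REM time, heart rate, step count, distance, device usage, and calls and texts. Age and sex are not among them.

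Three other places give age and sex a role:
- **Methods, Design, Overview:** "Participants in both groups will be matched for age and sex, since both can be confounding factors regarding usage patterns of electronic devices".
- **Table 1, questionnaire part:** STAI scores run from 0 to 60, "which are then transformed into percentiles according to age and sex". For AUDIT, "a score of ≥13 in women or ≥15 in men is likely to indicate alcohol dependence".
- **Initial In-Person Visit:** age and gender are among the variables to be measured, and participants open a Fitbit account and are told "to specify their age, sex, weight, height, and date of birth".

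The article does not say whether step 2 predicts the 0-60 STAI score or the percentile.

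**The concern.** Device usage, calls and texts are model inputs, and the plan itself names age and sex as possible confounders of device use. Matching makes the two groups alike on age and sex, so neither can create the difference between cases and controls. The primary outcome, however, is prediction of scores across participants. Cases may be anywhere from 18 to 70 years old, with controls matched to them, so age and sex still vary among the 60 people whose scores are estimated.

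What that variation does depends on the target:
- **Raw STAI, BDI-II or AUDIT score:** if the score is related to age or sex, a sensor that merely tracks age or sex will appear to predict symptoms.
- **Age- and sex-normed STAI percentile:** demographic variation is taken out of the target but left in the predictors, where it acts as noise and lowers apparent performance.

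Either way, a sensor-only performance figure on its own cannot show how much information the sensors carry beyond two facts already on file for every participant. That matters for a study whose Introduction aims at knowledge about digital biomarkers.

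**Working it through.** The article gives no effect size, variance share, error rate or accuracy target, so there is no stated figure to reproduce. What can be checked is whether the mechanism exists and how it behaves. All coefficients below are assumptions, shown as ranges.

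**Set-up.** Let S be the symptom score, A a single age/sex index, and X = b·S + g·A + error a sensor feature, all standardised to variance 1, with r = corr(S, A). Then corr(X, S) = b + g·r and corr(X, A) = g + b·r. R² for S is:
- sensor only: (b + g·r)²
- age/sex only: r²
- both: [(b + g·r)² + r² − 2·r·(b + g·r)(g + b·r)] / [1 − (g + b·r)²]

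**Normed target (r = 0).** Sensor-only R² is b², and with age/sex it is b²/(1 − g²).

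| b | g | sensor only | sensor + age/sex |
|---|---|---|---|
| 0.5 | 0 | 0.25 | 0.25 |
| 0.5 | 0.3 | 0.25 | 0.25/0.91 = 0.275 |
| 0.5 | 0.5 | 0.25 | 0.25/0.75 = 0.333 |
| 0.5 | 0.6 | 0.25 | 0.25/0.64 = 0.391 |
| 0.3 | 0.3 | 0.09 | 0.09/0.91 = 0.099 |
| 0.3 | 0.5 | 0.09 | 0.09/0.75 = 0.120 |
| 0.3 | 0.6 | 0.09 | 0.09/0.64 = 0.141 |

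With g = 0 nothing changes.

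**Target related to age/sex, sensor with no symptom link (b = 0, g = 0.5).** Sensor-only R² is (g·r)². Adding the sensor to age/sex leaves R² at r², a gain of 0.

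| r | sensor only | age/sex only | gain from sensor |
|---|---|---|---|
| 0.2 | 0.10² = 0.010 | 0.04 | 0 |
| 0.3 | 0.15² = 0.0225 | 0.09 | 0 |
| 0.5 | 0.25² = 0.0625 | 0.25 | 0 |

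**With the matched design.** A simulation of 30 cases and 30 controls matched on A (group shift 1.5 SD, 4000 replicates, in-sample R²) gave:
- b = g = 0.5, within-group corr(S, A) = 0: mean R² 0.35 for the sensor alone and 0.45 with age/sex.
- b = 0, g = 0.5: sensor-only mean R² rises from 0.015 at within-group correlation 0 to 0.029 at 0.3. The gain over age/sex is the same in both cases (0.028 − 0.011 = 0.017 and 0.081 − 0.064 = 0.017), which is only the overfitting from one useless predictor.
- The mean correlation of A with group was 0 throughout, which confirms that matching protects the case-control contrast.

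So both effects survive matching, and the gain over age/sex tells a sensor with symptom information from one without.

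**The case against.** The strongest defence is that sensor-only prediction is the declared question. The study asks whether sensor data could stand in for questionnaires, and a prediction model need not adjust for confounders to be valid. That stands, and it is why the sensor-only model should not be replaced or demoted.

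Several stronger readings are tempting but not supported:
- A reader might infer that a sensor-only model cannot deliver an age- and sex-normed percentile. It can: the norming is applied to the questionnaire score, and a model fitted to percentiles outputs percentiles. The fit may be poorer, nothing more.
- A reader might infer that the plan regards age and sex as determining device use. It says only "since both can be confounding factors regarding usage patterns of electronic devices", and it says nothing of the kind about heart rate or sleep.
- A reader might infer that the plan excludes covariates throughout. The restriction qualifies step 2 only; step 1 is left open.

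Other points limit the size. In a pooled case-control sample much of the score variation is likely to be the group contrast, which matching separates from age and sex. In the matched simulation the false signal is small (0.015 to 0.029). Age and sex hardly change during follow-up, so they cannot confound week-to-week change within a person. A single index A serving both sensor and score gives an upper bound: if different combinations of age and sex predict each, less carries over. Fitbit outputs may already use the age and sex entered in the account, which the article does not settle.

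**Conclusion.** The point holds in a limited form. Step 2 fixes a sensor-only model as the sole basis of the primary outcome, while the plan treats age and sex as possible confounders of some inputs and norms one target by them. Matching does not remove that variation within the groups, so the reported performance may be partly demographic or may be diluted by demographics. Which of the two applies to STAI depends on a target scale that the article leaves open.

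The documents do not allow the size to be derived. Over the assumed ranges, dilution takes R² from between 0.275 and 0.391 down to 0.25 (b = 0.5), and false signal amounts to R² of about 0.01 to 0.06. Both vanish if the sensors do not vary with age or sex. The documents do not support calling the primary analysis invalid. This is a cheap improvement.

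**What to change.** Keep the sensor-only model as the declared primary analysis. Add to the primary outcome section:
1. an age/sex-only model as a benchmark;
2. a sensors-plus-age/sex model, with the sensors' contribution reported as the gain in performance over the benchmark;
3. a statement of whether STAI is predicted as the 0-60 score or as the percentile.

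All three models should use the same participants and the same method of assessing performance, because in-sample R² rises by about 0.017 in the simulation even for a useless sensor.

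The cost is a little extra analysis and two more model parameters. No new data are needed: age and gender are among the first-visit variables, and the article reports that the data were still being processed.
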